### **17.1 Reporting to research ethics committee**

Any SAE occurring to a research participant will be reported to the main Rec (i.e. the rec that gave a favourable opinion of the study) where in the opinion of the chief investigator (CI), the event was:

- “related” – that is, it resulted from administration of any of the research procedures, and
- “unexpected” – that is, the type of event is not listed in the protocol as an expected occurrence.

Reports of related and unexpected SAEs should be submitted to the rec within 15 days of CI becoming aware of the event, using the ‘report of serious adverse event form’ for Non-CTIMPS published on the national research ethics service (nres) website.

<http://www.nres.npsa.nhs.uk/applications/after-ethical-review/safetyreports/safety-reports-for-all-other-research/> the form should be completed in typescript and signed by the CI (or designee). The sponsor’s office will assist in the preparation and submission of the report. to the main rec who will acknowledge receipt of safety reports within 30 days.

### **17.2 Annual progress report**

The CI or designee is also responsible for providing an annual progress report to the rec using an nres “annual progress report form for all other research”. this form is available at:

<http://www.nres.npsa.nhs.uk/applications/after-ethical-review/annual-progress-reports/> a section on the safety of participants is included in this report. The QMUL office will assist in the collation of the safety information required for the report. Reporting to local research and development (R&D) departments the principal investigator at each site is responsible for the provision of reports to their local R&D department per the conditions of management approval.

## **18.0 Laboratory aspect of the research**

All blood biomarkers will be managed and reported at specific study sites were possible following their SOPs and guidelines in accredited biochemistry and haematology laboratories Guys and St Thomas’s NHS Trust London, Addenbrookes Cambridge University Hospital, Cambridge and Barts Hospital NHS Trust, London and William Harvey research institute [name], London.

The 24 -hour urine steroid profile will be assayed and reported by the University of Birmingham as agreed by Sponsor’s Technical Agreement devised by the sponsor. These will be transferred for analysis using accredited Human tissue transfer courier.

Plasma samples will require 2mls whole blood collected in EDTA spun at 300xG (RCF) and then aliquoted into 1.5ml Eppendorf tubes then frozen at - 80°C. For serum sample, 3mls of blood will be drawn and when clotted the serum will be aliquoted into 1.5 Eppendorf tubes and frozen -80°C. Both Plasma and serum samples will be transferred to Queen Mary University of London at the end of the study following the Sponsors Technical Agreement.

Following adrenalectomy tissue will be genotyped for somatic mutations in *KCNJ5*, *ATP1A1*, *ATP2B3*, *CACNA1D*, *CTNNB1* and phenotyping by histological grading, gene expression and immunohistochemistry. Routine analyses (histology, some of the immunohistochemistry) will

be performed by the endocrine pathologist in the hospital where the patient has surgery, and photographs retained for central, blinded re-analysis by the study endpoints committee. If the tests are not available in the hospital where surgery was performed, tissue will be transferred to either Addenbrookes Hospital Cambridge, or to Barts Hospital, or Queen Mary University London. Non-routine analyses (e.g. genotyping, gene expression) will be performed at William Harvey Research Institute QMUL [name] London. Using fresh-frozen, RNAlater or paraffin section prepared at the time of surgery and stored at the local hospital until batched transfer to the site of analysis.

## **19.0 Statistical Aspect of the research**

Patients will receive AVS and  $^{11}\text{C}$  metomidate PET CT in ‘pseudo-random’ order. In order to allow for patients and situations where it is logistically easier to perform one investigation before the other – e.g. when the  $^{11}\text{C}$ -metomidate synthesis fails, and cannot be re-booked before an already scheduled AVS – we will use a minimization rather than randomisation procedure. This is a computer based programme which assigns order to each patient such that the difference in number of patients having one investigation first is minimized, but allows for the recommended order to be over-ridden. When eligibility has been confirmed, the order in which the diagnostic tests are to be performed will be obtained via the study web portal. The minimisation schedule will be stratified by study site. The minimisation schedule will be stored in a secure area of the Robertson Centre for Biostatistics network, with access restricted to those responsible for the randomisation system. Researchers at study sites will not know the order of tests until after baseline assessments have been carried out, and statisticians at the Robertson Centre will not have access to the minimisation schedule until the end of the study, when all analysis programs have been written and verified.

## **20.0 Study Outcomes**

### **20.1 Primary Outcome(s)**

1. Change in ARR from baseline to 6 months after surgery, or 9-12 months after MDT in patients not proceeding to surgery. (For patients whose surgery takes place less than six months prior to overall study-end, data will be used from the 3 month post-op visit, or the six-month visit will be brought forward. This qualification applies to all other reference to the six-month visit and data in this protocol.)
2. Change in SBP (mean of at least 12 measurements from 3 days home monitoring), from baseline to 6 months after treatment, or 9-12 months after MDT in patients not proceeding to surgery

### **20.2 Secondary Outcomes**

A number of pre-specified pre-operative radiological parameters, and post-operative histological, immunohistochemical, molecular and genetic measurements will be compared between patients

whose [i] ARR and [ii] blood pressure are normalized by surgical or medical treatment.

1. Cure of hypertension, defined as the proportion of patients in whom average home blood Pressure measurements 6 months post adrenalectomy are <140/90 mmHg on no treatment.
2. Prediction of cure of hypertension, by one or more of:
  - a) The ratio of SUVmax between tumour and normal adrenal;
  - b) Blood pressure fall on spironolactone/eplerenone (50 mg daily for 2 weeks, 100 mg daily for 2 weeks), measured as the difference in home systolic blood pressure
  - c) Post-operative analyses of the APA, to include genotyping for somatic mutations in KCNJ5, CACNA1D, ATP1A1, ATP2B3, CTNNB1 and phenotyping by histological grading (zona fasciculata versus zona glomerulosa), gene expression and immunohistochemistry.
3. Change in home blood pressure from baseline at follow-up visits other than 6 months post-adrenalectomy.
4. Reduction in number of antihypertensive drugs
5. Change from baseline in blood levels of Troponin, Brain Natriuretic Peptide.
6. Cardiac MRI changes in heart structure, anatomy and blood flow from baseline to six months.
7. Changes in Quality of life from baseline to six months.
- 8 Change in baseline serum cortisol and salivary cortisol measurements at 3 months post adrenalectomy.

The judgement as to which patients have met primary and secondary outcomes will be made by a critical endpoints committee meeting every 3-6 months throughout the study.

## **21.0 Planned Methods of Analysis**

The planned study analyses will be detailed in the study-specific Statistical Analysis Plan (SAP), which will be finalised in advance of study closure.

The primary outcomes will be analysed in a hierarchical manner:

1. Change in ARR, between baseline and 6 months post-surgery (or equivalent time-point relative to baseline if no surgery), comparing patients who have surgery with patients who do not have surgery.
2. Blood pressure cure rates (home SBP < 135 mmHg on no antihypertensive treatment), comparing patients who have surgery with patients who do not have surgery.
3. ARR in patients who have surgery but have discordant AVS and PET-CT results, comparing patients whose surgery was indicated by high probability PET CT with patients whose surgery was indicated by high-probability AVS.
4. Blood pressure cure-or-control rates (home SBP =20 mm Hg or DBP =10 mm Hg lower than prespironolactone/eplerenone, i.e. baseline) in patients with discordant AVS and PET-CT results, comparing those whose surgery was indicated by high-probability PET CT with patients whose surgery was indicated by high-probability AVS.

5. Blood pressure cure rates (home SBP < 135 mmHg on no antihypertensive treatment) in patients with discordant AVS and PET-CT results, comparing those whose surgery was indicated by high-probability PET CT with patients whose surgery was indicated by high-probability AVS.

## **22.0 Safety Analysis.**

Safety evaluation will include all patients in the Safety Population, and will be descriptive in nature.

### **22.1 Interim Analysis**

There are no planned interim analyses.

### **22.2 Final Analysis**

The final study analysis, as detailed in the SAP will be carried out after study closure and the study databases have been finalised and locked.

## **23.0 Sample Calculation**

The calculations on sample size are based on our stated intention that AVS will only be performed in centres whose robust audit data indicate a bilateral cannulation rate of  $\geq 75\%$ , as the testing of the hypothesis will have maximum clinical value if  $^{11}\text{C}$  metomidate scanning is compared with current best practice AVS. It also assumes that 100% of metomidate scans will provide a technically satisfactory result (we consider this to be reasonable, based on the Cambridge experience since the investigation was first introduced in May 2009).

The design of the study (and therefore the statistical analysis) presupposes that there will be a group of patients for whom the results from metomidate scanning and AVS will differ, but that the former is correct more often and that this difference is statistically significant. Given the results of the proof-of-concept study, it is inevitably the case that there will be a large group of patients for whom the two tests are concordant. The different scenarios of concordant/discordant, unilateral/bilateral, together with their estimated frequencies, are shown in Appendix, and it is these figures that have been used by the Clinical Trials Unit in Glasgow as the model for the sample size calculation and proposed analysis.

Recruitment of 165 patients across 3 centres over 3 years (<1/centre/month), with an estimated 70 proceeding to adrenalectomy, permits 90% power at  $\alpha=0.01$  of detecting non inferiority of PET CT in relation to AVS within a margin 16.7%. Based on the current size of referral practices at each centre, we are confident of meeting the recruitment target.

There will be a sub-study of 6 patients who will have a 11-C metomidate PET CT scan before and following spironolactone/eplerenone therapy. In our previous study, the uptake of metomidate into tumour was 60% greater than contralateral normal adrenal (mean(SD) = 21.7(8.0) vs 13.8 (3.0)). The study of six patients on two occasions will give us 90% power to detect just 30% increase in normal adrenal uptake, even if there is no parallel increase in tumour uptake of metomidate ( $\alpha=0.05$ , one-sample test).

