|                    |                                                                                                                                                                                                                                                                                                                                                                                                                                                                                                                                                                                                                                                                                          |
|--------------------|------------------------------------------------------------------------------------------------------------------------------------------------------------------------------------------------------------------------------------------------------------------------------------------------------------------------------------------------------------------------------------------------------------------------------------------------------------------------------------------------------------------------------------------------------------------------------------------------------------------------------------------------------------------------------------------|
| Sample Size | 
The sample size calculation has been performed to permit detection of a significant influence on outcome where the smallest number of patients will be available. This is the group of patients in whom the two diagnostic techniques give discordant results, estimated to be ~20% of the total.
 
Recruitment of 165 patients across 3 centres over 3 years (<1/centre/month), with an estimated 90 proceeding to adrenalectomy, permits 90% power at <math>\alpha=0.01</math> of detecting superiority of all hierarchical primary outcomes. This sample size will also provide 90% power to show non inferiority of PET CT in relation to AVS within a margin of 18%.
 |

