### **12.1 Trial Sites and Numbers of Participants**

A total of 165 patients will be recruited into the study, from approx. three to six study sites within the UK depending on success on patient recruitment. Recruitment will continue until at least 70 patients have proceeded to adrenalectomy, even if we exceed a total of 165 patients being consented and undergoing investigations. This allows for some patients who may withdraw between consent and completion of investigations and/or surgery.

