## **2.3. EFFICACY OUTCOMES**

### **2.3.1. PRIMARY OUTCOMES**

The primary outcomes will be analysed hierarchically. If the first primary analysis is statistically significant at  $p < 0.05$ , then the second primary outcome will be analysed; if the second primary analysis is statistically significant at  $p < 0.05$ , then the second primary outcome will be analysed; and so on. If any primary analysis fails to reach  $p < 0.05$ , then subsequent analyses will be considered secondary analyses.

Each primary outcome will be analysed in the subgroup of FAS patients who undergo surgery.

- Cure of hypertension at 6 months (non-inferiority analyses)
  - comparing accuracy of AVS and 11C-Metomidate PET-CT
  - each scan judged to be accurate if it indicated unilateral disease and cure of hypertension was achieved after surgery, or if the scan did not indicate unilateral disease and cure was not achieved after surgery
  - report estimated difference in accuracy (Newcombe-Wilson method for paired data) between 11C-Metomidate PET-CT and AVS, with 95% CI
  - non inferiority of 11C-Metomidate PET-CT will be declared if the lower limit of the above 95% CI is greater than -17%
  - each measure of cure (see Section 1.8) will be analysed in turn
- Cure of hypertension at 6 months (superiority analyses)
  - in addition to above, report p-value from exact McNemar test
  - superiority of 11C-Metomidate PET-CT will be declared if  $p < 0.05$ , and the lower limit of the 95% CI is greater than 0%

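### The synopsis and section 23 give conflicting non-inferiority margins and operation counts for the same 165 recruits, and 90% power at equal accuracy rests on a discordant share lower than the protocol's table implies for operated patients

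*Combined protocol and SAP*

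**What the plan says.** Three places deal with non-inferiority of PET-CT to AVS.

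- **Protocol synopsis, Sample Size.** 165 recruits, "with an estimated 90 proceeding to adrenalectomy". After a superiority statement at alpha=0.01 it adds: "This sample size will also provide 90% power to show non inferiority of PET CT in relation to AVS within a margin of 18" percent. The non-inferiority sentence names no alpha. Discordant results are put at about 20% of all patients.
- **Protocol section 23.** The same 165 recruits, "with an estimated 70 proceeding to adrenalectomy, permits 90% power". The level is given as alpha=0.01, and section 23 describes this as the power "of detecting non inferiority of PET CT in relation to AVS within a margin 16.7" percent. Of the appendix table (section 33) it says: "it is these figures that have been used by the Clinical Trials Unit in Glasgow as the model for the sample size calculation". Section 12.1 makes the lower count a floor: "Recruitment will continue until at least 70 patients have proceeded to adrenalectomy".
- **SAP 2.3.1.** Each primary outcome is analysed in Full Analysis Set patients who undergo surgery, and "non inferiority of 11C-Metomidate PET-CT will be declared if the lower limit of the above 95% CI is greater than -17" percent, by the Newcombe-Wilson paired method. SAP 1.5 reproduces only the superiority calculation. It gives no power for non-inferiority.

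None of the three states the discordant share among operated patients, the true accuracy difference, or the sidedness of the 1% level behind the non-inferiority power.

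**The concern.** For a paired comparison at fixed power, alpha, discordance and true difference, the margin that can be supported shrinks as the number of operations grows. The synopsis has more operations and a wider margin; section 23 has fewer and a tighter one. Both belong to the current protocol and describe the same 165 recruits.

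Power at equal accuracy also depends heavily on how often the two tests disagree in the patients analysed. Restricting the analysis to operated patients drops the large group negative on both tests, so the discordant share rises. A share of all patients used in its place overstates power.

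Non-inferiority is tested on every primary outcome. If the tests are about equally accurate, the chance of missing non-inferiority could be well above the 10% a reader takes from the stated power.

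**Working it through.** **Inputs from the protocol table (section 33; percent of all patients)**

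- Cells leading to surgery: C 1 + D 10 + G 1 + H 9 + I 0.5 + J 3.5 + K 1 + L 29 + M, O, P, Q 0.25 each = 56.
- Tests disagree, AVS conclusive: G+H+I+J+M+O+P+Q = 15.
- With failed AVS counted (adding D 10): 25, of which 20 favour PET-CT and 5 favour AVS.
- Share of operated patients: 15/56 = 26.8%, or 25/56 = 44.6%. SAP 2.3.1 scores a failed AVS as not indicating unilateral disease, so the higher figure is closer to its primary analysis. Read literally, that rule also credits AVS in cell C, giving 26/56 = 46.4%.

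**Formulas**

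With n operations, discordant share ψ, true difference d and margin m:

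- SE = √((ψ − d²)/n)
- Power = Φ((d + m)/SE − z)
- At d = 0, margin for 90% power = (z + 1.282) × √(ψ/n)

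**Reproducing the plan's figures (d = 0)**

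- Section 23: n=70, ψ=0.15, one-sided 1%: (2.326 + 1.282) × √(0.15/70) = 3.608 × 0.0463 = 16.7%. This matches.
- Synopsis: n=90, ψ=0.20, two-sided 1%: (2.576 + 1.282) × √(0.20/90) = 3.857 × 0.0471 = 18.2%; power at 18% is 89.3%. This matches approximately.

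Both routes are inferred, since the documents do not state them.

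**The two statements against each other**

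- Section 23's assumptions with 90 operations: 16.7% × √(70/90) = 14.7%, not 18%.
- The synopsis's assumptions with 70 operations: 18% × √(90/70) = 20.4%, not 16.7%.
- Alpha alone does not reconcile them. At ψ=0.15, n=90 and 18%, 0.18/0.0408 = 4.41 and 4.41 − 1.28 = 3.13, a one-sided level of about 0.0009, which appears nowhere.

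**Using the discordant share among operated patients (d = 0)**

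Section 23, n=70, margin 16.7%, one-sided 1%:

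- ψ=26.8%: SE = 0.0619; 0.167/0.0619 = 2.70; Φ(2.70 − 2.326) = 65%.
- ψ=44.6%: SE = 0.0799; 0.167/0.0799 = 2.09; Φ(2.09 − 2.326) = 41%.

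At two-sided 1% these become 55% and 31%. For the synopsis (n=90, 18%, two-sided 1%) they are 77% and 49%.

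**The SAP's own rule (Newcombe paired 95% interval, −17%), simulated at equal accuracy**

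| Discordant share in operated patients | 70 operations | 90 operations |
|---|---|---|
| 20% (share of all patients, for comparison) | 86% | 94% |
| 26.8% | 77% | 87% |
| 44.6% | 59% | 68% |

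Repeat runs and the split of concordant patients move these by about a point. At 46.4% the results are about 57% and 67%.

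**The table's own PET-CT advantage**

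Under the SAP accuracy rule, d = (20 − 6)/56 = 25.0 points and ψ = 26/56. With n=70 and 16.7%, SE = √((0.464 − 0.0625)/70) = 0.0758; (0.25 + 0.167)/0.0758 = 5.50; power is 99.9% at one-sided 1%. Simulating the SAP rule also gives above 99.9%.

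**The case against.** A reader might infer that 90% power is simply not delivered. The documents do not support that. Section 23's margin reproduces exactly on one coherent set of inputs. Section 23 also names the table as its model, and in that table PET-CT is the better test, so power exceeds 99%. The low figures keep the table's discordance but remove its direction, and much of that discordance exists because PET-CT is assumed better (D and H supply 19 of the 25 points). A modest advantage recovers power: at 44.6% discordance, 70 operations and the SAP's rule, the normal approximation gives Φ((0.10 + 0.17)/√((0.446 − 0.01)/70) − 1.96) = 93% for a true 10-point advantage. This stands, and it rules out printing one low figure as the delivered power.

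A reader might also infer that three margins are mutually impossible. That overreaches. The SAP's 17% may be 16.7% rounded, it carries no power claim, and SAP 1.10.3 declares departures from the protocol and a planned amendment. Nor does 20% versus 44.6% show an error in the synopsis: the denominators differ, and the like-for-like gap is 20% versus 25% of all patients.

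The formal sample size is the superiority test, so non-inferiority is not what fixed the 165. That is true, but the SAP makes non-inferiority part of every primary analysis and the protocol attaches a power to it.

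What the objection does not answer is the conflict between synopsis and section 23, the change from alpha=0.01 to a 95% interval, and the use of all-patient discordance for an operated-only analysis.

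**Conclusion.** The conflict between the synopsis and section 23 is firm: 90 operations at 18% and 70 at 16.7% cannot share one set of assumptions. The SAP adds a different confidence level and no power.

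The stated 90% is conditional. It holds at equal accuracy only if the discordant share among operated patients is about 15% (section 23, one-sided 1%) or 20% (synopsis, two-sided 1%), where the table implies 26.8% to 44.6%. With those shares and equal accuracy, the chance of missing non-inferiority under the SAP rule is about 23% to 41% with 70 operations and 13% to 32% with 90. If the table's PET-CT advantage is real, it is below 1%. These sizes rest on the table's cell estimates and on the true difference chosen; the documents do not say which difference was used.

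**What to change.** In the synopsis, section 23 and SAP 1.5/2.3.1:

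1. Use one margin (the SAP's 17 points), one confidence level with its sidedness, and one expected number of operations.
2. Replace the unconditional 90% power for non-inferiority with power under the SAP rule. State beside it the discordant share among operated patients, how failed AVS is counted, and the assumed true difference.
3. Show power both at equal accuracy and under the table's assumed PET-CT advantage, labelled as conditional scenarios.

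The cost is wording, which can go into the protocol amendment that SAP 1.10.3 already plans. No extra patients are needed. The downside is a less favourable stated power at equal accuracy.
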